**Figure 2 j_med-2023-0814_fig_002:**
[figure not shown]
Intervention and assessment schedule per group allocation.

### Intervention

2.5

Depending on the group, participants will receive iTBS (or sham) intervention 4 times per week for 1, 2, or 4 weeks. Each intervention session will last around 30 min, including 20 min of iTBS. The iTBS (or sham) sessions will be delivered by two TMS operators that completed 15 h of training to deliver TMS. The sessions will be conducted in a private and quiet room located at the Clinical Research Facility of Nottingham University Hospitals. The first intervention session will be scheduled for weeks 2, 4, or 5 depending on the group. We designed this study to have, for all participants regardless of group allocation, a 5-week standardised gap between baseline assessment on week 1, administrated before any iTBS session and the EOI assessments on week 5, administrated immediately after the last iTBS session.

#### iTBS intervention

2.5.1

For participants allocated to one of the real iTBS groups, stimulation will be administered to the DLPFC target coordinates (see below for target identification) under StimGuide neuronavigation using a 70 mm Double Air Film Coil (Magstim, Whitland, Dyfed, UK), connected to a Magstim Horizon Performance stimulator. The administration comprises bursts of 3 pulses at 50 Hz with a power of 80% of the resting motor threshold (RMT), at a burst frequency of 5 Hz (i.e., every 200 ms) for 2 s, repeated every 10 s for a total of 190 s (600 pulses) [28]. Blocks will be repeated a total of 3 times, with 5-min rest intervals between blocks, a total of 1800 pulse per treatment session. During left DLPFC stimulation, the iTBS coil is held by support tangentially to the skull, with the axis of the coil angled approximately 45° from the midsagittal plane. The total duration of each administration is approximately 20 min.

#### Sham intervention

2.5.2

The sham iTBS administration will be performed under the same conditions and with an identical protocol including 50% RMT and equipment to the full administration, except that the 8-shaped iTBS coil is held orthogonally to the scalp surface, its side touching the scalp to provide a similar sensation of direct contact to the real intervention, with the axis of the coil parallel to the midsagittal plane. The centre of the coil is kept roughly 10 cm from the skull and does not deliver any stimulation in the direction of the cortical surface. The sound made by the iTBS coil is the same as the real intervention stimulation. The TMS operators display a sham coil position on the screen of the neuronavigation system, similar to that shown for the real intervention.

### Study procedures and data collection

2.6

Study data will be collected and managed using REDCap electronic data capture tools [29,30] hosted at the University of Nottingham.

#### Initial participant screening

2.6.1

Screening procedures will be conducted via telephone or videoconference by the research psychologist. The oral version of the SDMT and the PHQ-9 will be administered. Participants will be asked to complete a questionnaire regarding their demographics, MS diagnosis, and current treatments and to identify possible contraindications to MRI and TMS procedures.

Patients fulfilling the eligibility criteria will be invited to participate in the trial. Those who do not meet eligibility criteria will be excluded and thanked for their time. Reasons for ineligibility will be recorded.

#### Demographic and clinical characteristics

2.6.2

Following enrolment, missing information regarding the participants’ clinical characteristics (e.g., type of MS, years with MS, years with symptoms suggestive of MS, medications) will be requested from the neurologist or usual MS care team, along with the participants’ most recent Expanded Disability Status Score [31]. The use of disease-modifying treatment by recruited participants will be recorded and reported.

#### Baseline assessments and MRI scan

2.6.3

All participants regardless of group allocation will complete the following procedures at baseline assessment in week 1.

Participants will undergo in-person baseline cognitive and mood assessment that includes:The Brief International Cognitive Assessment for MS (BICAMS): The BICAMS was developed by an international panel to support a cognitive assessment that is brief and universal, to include tests of mental processing speed and memory. It was developed to be optimised for small centres where staff may not have formal neuropsychological training [32]. Tests included are:
The SDMT, assessing attention, working memory, and visual/spatial information processing speed [33].The California Verbal Learning Test-II, assessing verbal memory recall [34].The Brief Visuospatial Memory Test Revised, assessing visual memory [35].
Digit Span (from WAIS-IV): this test comprises two conditions, namely Digit Span Forwards (DSF) and Backwards (DSB). DSF assesses attention, encoding, and auditory processing capacity while DSB assesses working memory and executive function [36].Patient Health Questionnaire (PHQ-9) is a module of the PHQ for recording severity of depressive symptoms [26] and has been validated in primary care populations [37,38].Generalised Anxiety Disorder (GAD-7) is a brief scale to screen for generalised anxiety disorder [39].The Perceived Deficits Questionnaire (PDQ) assesses subjective cognitive dysfunction in people with MS [40]. The PDQ includes four subscales (attention/concentration, retrospective memory, prospective memory, and planning/organization).The Modified Fatigue Impact Scale (MFIS) is a self-report questionnaire exploring the effects of fatigue across physical, cognitive, and psychosocial modalities. It is a modified form of the Fatigue Impact Scale [41] and was developed following interviews with people with MS who discussed how fatigue had impacted their daily lives.The Edinburgh Handedness Inventory (EHI) assesses whether participants favour their left or right hand to inform the MRI analysis.

Participants will have a 3T MRI scan to allow target localisation, quantification of MS lesion burden, and characterisation of brain networks and connectivity. The MRI scan will include:High-resolution T1-weighted volume, for image co-registration and segmentation;Resting-state functional MRI, for functional connectivity analysis;Fluid-attenuated inversion recovery, for MS T2 lesion quantification;Diffusion tensor imaging, for structural connectivity analysis;

The T1-weighted and resting state functional MRI will be used to estimate the iTBS intervention targets.

#### Intervention visits

2.6.4

Two working days before the participants’ first visit, staff delivering the iTBS (or sham) intervention will ask participants if anything has changed since they were assessed which may impact their cognitive abilities, such as infection or MS relapse. If they have MS relapse or active/recent infection, they will be withdrawn from the study.

The first iTBS (active or sham) session will begin with the estimation of the RMT as detected using electromyography (EMG) to record a motor response in the contralateral abductor pollicis brevis. This is achieved by administration of single pulses of TMS to the scalp over the approximate location of the primary hand motor area of the left hemisphere, identified using the StimGuide neuronavigation system to locate the C3 position on the scalp. Slight adjustments to the position of the coil and the angle relative to the scalp surface are made by the operator to optimise stimulation of the primary hand motor area. The TMS operator delivers single TMS pulses with varying intensities guided by the adaptive Parameter Estimation by Sequential Testing [42] to estimate the participant’s RMT, defined as the minimum TMS intensity sufficient to produce a >50 μV motor‐evoked potential recoded by EMG in at least 50% of trials [43].

The localisation of the left DLPFC target will be identified using a similar target-identification methodology to previous work [23,44], using effective connectivity of the left caudate to identify the maximally connected locus in the left DLFPC.

The participant then receives the intervention according to group allocation as described above in the ‘Intervention’ section.

Following each administration, the participant is asked to report any sensations they may have experienced.

In case of missed appointments, the research team will work with the participant to reschedule the appointment, providing that participants do not have more than four consecutive days without intervention (including weekends) and that the total afforded extra time does not exceed 50% of the initial intervention schedule.

Thus, participants allocated to 1 week of intervention (group 1) will be allowed 3 extra days within which to complete the intervention schedule. Participants allocated to 2 weeks of intervention (groups 2 and 4) will have one extra week to complete it and participants allocated to 4 weeks of intervention (group 3) will be afforded up to 2 weeks during which to complete it. If the intervention cannot be administrated during the allowed time, this will be recorded as a protocol deviation.

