### Study aim

2.1

This study will test the feasibility and acceptability of iTBS as an intervention for improving cognitive performance in people with MS. Group allocation will allow comparison of feasibility and acceptability of iTBS administration schedules of different total durations (1, 2, and 4 weeks) and assessment of the believability of the sham administration, which will inform the design of a phase III trial which will investigate the clinical- and cost-effectiveness of the treatment.

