**Figure 1 j_med-2023-0814_fig_001:**
[figure not shown]
Trial flowchart.

Consenting procedures will be conducted by the research psychologist. Participants will be randomised after completing the consent form, and the research psychologist will be blinded to group allocation. Participants will be randomised to one of four groups in equal proportions (1:1:1:1 ratio) automatically using blocked stratified randomisation, stratified on: age group (≤40), gender (man or woman), and MS type (relapsing-remitting MS or secondary progressive or primary progressive MS). The randomisation schema was created on 9th November 2021 10:51 using *ralloc.ado* version 3.5.2 [27] in Stata version 17. The neuromodulation research fellow is notified of the group allocation via an automatic email. The research psychologist and principal investigator will remain blinded to group allocation. The two TMS operators (including the neuromodulation research fellow) administering the iTBS will not be blind to group allocation.

Participants will be blinded as to whether their iTBS intervention is real (groups 1, 2, and 3) or sham (group 4) until the end of their study participation. Although only the 2-week intervention duration has a sham comparator (group 2 = real iTBS, group 4 = sham iTBS), participants will not be made aware that the 1- and 4-week intervention durations do not have a sham comparator. Participants will be instructed not to tell the research psychologist the duration of their intervention, as this would reveal to the research psychologist that the patient received the real iTBS intervention if in the 1- or 4-week intervention groups. To standardise the assessment interval and maintain the blinded status of the research psychologist, the interval between baseline and EOI assessments will be fixed at 5 weeks, requiring commencement of the iTBS intervention to be staggered per group as per Figure 2.

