#### Early withdrawal interviews

2.6.7

As this is a feasibility trial, participants withdrawing from the study before completing the protocol will be invited for an exit interview to explore the reasons for withdrawal.

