### Endpoints measured

2.7

As this is a feasibility study several endpoints will be collected to allow primary and secondary aims to be assessed, shown in Table 1.

**Table 1 j_med-2023-0814_tab_001:** Feasibility trial endpoints

Endpoints to address the primary objective
Proportion of screened potential participants eligible for participation
Proportion of eligible potential participants consenting for participation
Number of participants completing the visit schedule as per protocol
Questionnaire ratings of tolerability of the iTBS or sham administration
Questionnaire ratings of overall acceptability of trial participation
Number and type of adverse events
Participant opinion at EOT of whether they received real or sham iTBS

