### Data analysis plan

2.9

Data will be reported according to the CONSORT 2010 statement, extension for pilot and feasibility trials [46]. The research psychologist will perform the scoring cognitive tests and questionnaires scores and collation/tabulation of other endpoints prior to unblinded group analysis. Quantitative data will be analysed using SPSS version 24.0 [47]. We will provide descriptive statistics regarding the characteristics of the participants. Rates of consenting participants, recruitment, intervention completion, acceptability, tolerability, and adverse events will be reported by group on an intention-to-treat analysis (excluding participants who withdrew from the trial before the first iTBS administration).

Quantitative analysis will be used to evaluate the change in cognition, mood, and fatigue using the cognitive assessment and questionnaires. Where appropriate, parametric or non-parametric statistics will be used to estimate effect sizes and perform between-group comparisons to inform power and sample size calculations for a potential future phase III trial.

Qualitative data (post-intervention interviews) will be analysed using framework analysis [48–51]. These will be audio-recorded and transcribed verbatim by the research psychologist. The interview transcripts will be mapped onto a predefined framework. An analytical framework will be developed according to the interview schedule which will map onto the aims of the qualitative study. The researcher will read the transcripts to get familiar with the content of the interview. Subsequent analysis will be conducted on NVivo software [52]. This process will follow Gale et al.’s guide to framework analysis [48]. Following the initial coding of the first transcript, two researchers will meet to discuss the codes and to check whether the coding is consistent and comprehensive. Disagreements will be resolved through discussion together or with a third member of the study team to prevent bias. Once all the coding is completed, the researcher will enter these data onto the framework matrix and determine the fit of the data to this matrix. Any new data that does not fit the matrix will be considered again to see whether a new thematic structure is needed to include such data.

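### By-group rates labelled intention-to-treat omit randomised participants withdrawn at a pre-start illness check that falls 14 or 21 days later than in the 4-week group

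*Protocol article*

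**What the plan says.** Section 2.4 of the protocol article fixes the order of events: "Participants will be randomised after completing the consent form". Section 2.5 staggers the start: "The first intervention session will be scheduled for weeks 2, 4, or 5 depending on the group". The EOI assessment follows the last session in week 5 for every group.

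Section 2.6.4 places a check for relapse and infection two working days before the first visit, with this consequence: "If they have MS relapse or active/recent infection, they will be withdrawn from the study".

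Section 2.9 then reports consent, recruitment, completion, acceptability, tolerability and adverse-event rates "by group on an intention-to-treat analysis (excluding participants who withdrew from the trial before the first iTBS administration").

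The use of these rates is stated in section 2.1: "Group allocation will allow comparison of feasibility and acceptability of iTBS administration schedules of different total durations (1, 2, and 4 weeks"). Table 1 in section 2.7 lists among the primary-objective endpoints "Number of participants completing the visit schedule as per protocol".

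**The concern.** Leaving out non-starters is often harmless when failing to start has nothing to do with allocation. Here allocation sets how long a participant waits before a check that can end participation. An illness present in week 4 takes a group 1 participant out of the by-group rates. A group 3 participant with the same illness has already started and stays in, whatever happens next.

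Two things follow. The label intention-to-treat is wrong for a set from which randomised people are removed by an arm-dependent rule. And losses before the first session, which bear directly on the primary objective of judging whether the trial procedures are feasible, do not appear in the by-group rates. With up to 10 per group, one person is worth about 10 percentage points, and the comparison of schedules is meant to inform the phase III design.

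**Working it through.** **1. Start weeks.** Inputs: durations of 4, 2, 2 and 1 weeks for groups 3, 2, 4 and 1 (section 2.2) and EOI in week 5 (section 2.5). Start week = 5 − duration + 1, giving 2, 4, 4 and 5. This reproduces the stated weeks 2, 4 and 5. Figure 2 is not shown, but no other assignment fits.

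**2. Lag of the check behind group 3.** 7 × (4 − 2) = 14 days for groups 2 and 4; 7 × (5 − 2) = 21 days for group 1. Between group 2 and sham the lag is 0.

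**3. Direction, by example.** Assume Monday starts, so the group 1 check is on Thursday of week 4. Take 10 per group, one infection in each of groups 1 and 3, return to clinic on the next Monday, and everyone else completing. Section 2.6.4 allows rescheduling provided "participants do not have more than four consecutive days without intervention (including weekends").

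| Onset in week 4 | Group 3 days missed | Started set, group 1 v 3 | All randomised, group 1 v 3 |
|---|---|---|---|
| Wednesday | Wed–Sun = 5, over the limit | 9/9 v 9/10 | 9/10 v 9/10 |
| Thursday, Wednesday session given | Thu–Sun = 4, within the limit | 9/9 v 10/10 | 9/10 v 10/10 |

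In the first row the started set shows a gap that the all-randomised rate does not. In the second row it is the reverse. The denominators differ in both, but neither rate is the right one in general.

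**4. Size.** The documents give no event rate and no length for a recent infection, so everything here is assumed. Take baseline on Monday of week 1 as day 0, checks on days 3 (group 3), 17 (groups 2 and 4) and 24 (group 1), and EOI on day 32. Widening means the group 3 minus group 1 gap in non-completion on the started set, minus the same gap on all randomised.

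*Reading A: look-back of 7 or 14 days, but only back to baseline.* At 20% with an event over 32 days, the daily rate per 10 is 10 × 0.20/32 = 0.0625.
- Removed before start: group 3, 3 × 0.0625 = 0.19; groups 1, 2 and 4, 0.44 (7 days) or 0.88 (14 days).
- On treatment: group 3, 29 × 0.0625 = 1.81; group 1, 8 × 0.0625 = 0.50.
- If every on-treatment event blocks completion, started set: 1.81/9.81 = 18.5% v 0.50/9.56 = 5.2% or 0.50/9.12 = 5.5%, a gap of 13.2 or 13.0 points. All randomised: 20.0% v 9.4% or 13.8%, a gap of 10.6 or 6.2. Widening 2.6 or 6.7 points.
- If half of them block, started-set gap 6.6 or 6.5; all-randomised gap 4.1 or −0.3. Widening 2.6 or 6.8 points.
- At 10% over 32 days the widening is about 1.3 (7 days) to 3.4 (14 days) points.

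*Reading B: the same look-back applied in full at every check.* Removals are 0.44 or 0.88 per 10 in every group. At 20%, all blocking: started-set gap 13.7 or 14.4; all-randomised gap (1.81 − 0.50)/10 = 13.1. Widening 0.6 or 1.3 points.

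*Reading C: any event since baseline counts.* Removals per 10 = 10 × (1 − exp(−rate × days/365.25)). For groups 3 / 2 and 4 / 1 this gives 0.04 / 0.23 / 0.32 at 0.5 events per person-year, 0.08 / 0.45 / 0.64 at 1, and 0.16 / 0.89 / 1.23 at 2. If any event up to day 33 prevents completion and 10% fail for other reasons, then at 1 per year completion is 0.9 × exp(−33/365.25) = 82.2% in every group on all randomised, against 87.8% (group 1), 86.1% (groups 2 and 4) and 82.9% (group 3) on the started set. The widening is 87.8 − 82.9 = 4.9 points; at 2 per year it is 85.7 − 76.4 = 9.3 points.

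**The case against.** The strongest reply is that the started set answers a sensible question. A 4-week course is open to interruption for about four weeks and a 1-week course for one, and that is a real property of the schedules being compared. The wait in group 1 belongs to no 1-week schedule; it exists to standardise the assessment interval and protect the assessor's blinding. Counting illness during it as group 1 non-completion charges a design delay to the short course. The −0.3 point all-randomised gap above shows how far this can go: it hides the difference although group 3 has 1.81 on-treatment events per 10 and group 1 has 0.50. Ratings of session tolerability also cannot come from people who had no session. All of this stands, and it is why the all-randomised rate should accompany the started-set rate and not replace it.

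It can also be said that Table 1 lists completion as a count, which the denominator does not touch; that the article sets no completion threshold; and that reporting under the CONSORT pilot extension may show the losses anyway. These points lower the stakes. They do not change the set that section 2.9 fixes for the by-group rates, or its label.

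Finally, section 2.9 speaks of participants who withdrew and section 2.6.4 of participants who will be withdrawn. Taking the first to include the second is the natural reading; if the sponsor means otherwise, one sentence would settle it.

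**Conclusion.** The point holds as a matter of labelling and reporting. The timing follows from the article alone: the check comes 14 or 21 days later than in group 3, so inclusion in the by-group rates depends on the arm's wait. Group 2 versus sham shares a start week and is unaffected.

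The size cannot be fixed from the documents. Depending on how the check is read, the started set widens the group 3 versus group 1 gap by anything from about 1 point or less to several points. That is probably well under one participant per 10 and could be near zero; it approaches one only if every event since baseline counts and events are frequent.

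A reader might infer that the planned set biases the comparison against the 4-week schedule by a known amount. The documents do not support that: part of any gap is a true effect of a longer course, and moving onset by one day in the example removes the gap from the started set. A reader might also infer bias in cognitive change, or a serious loss of outcome data. Nothing here shows the former. The latter rests mainly on what a condensed article does not mention: for early leavers it says only that "participants withdrawing from the study before completing the protocol will be invited for an exit interview".

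**What to change.** In section 2.9:

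- Report completion by group with all randomised participants as the denominator, beside the rate among those who started treatment.
- Drop the intention-to-treat label from the started set and name it for what it is.
- Show non-starts due to relapse or infection as a separate line by group, so that losses during the design-imposed wait can be told apart from failure to complete the schedule.

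The cost is one extra table line. Allocation is automatic, so the all-randomised denominator should be available for everyone, including those already recruited. The drawback is that the all-randomised rate charges the wait to the shorter schedules, which is why both rates are needed.

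A minor extra would be to let the check decide only whether stimulation starts and to offer non-starters optional EOI and 8-week visits. On the status in section 2.12, this could reach at most (40 − 24) + (24 − 14) = 26 of 40 participants.
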